### Eligibility

#### Inclusion criteria

Participants in the study are 12–18-year-old children, in good general health;Children, requiring fixed orthodontic treatment (fixed braces);Children at high caries risk according to “Oral disease risk assessment tool” accepted and used in the Department of Paediatric Dentistry, Faculty of Dental medicine, Medical University – Plovdiv, Bulgaria (see supplementary data file S1 “Appendix for risk assessment of oral diseases”);Children with untreated non-carious vestibular surfaces of the six maxillary anterior teeth of the permanent dentition (central and lateral incisors, canines) with ICDAS code 0 [22–24];Verbal assent from the child willing to comply with all study procedures and protocol; andObtained written informed consent by the patient’s parent/guardian for participation in the study (see supplementary data file S2 “Patient consent form” and S3 “Information leaflet”).

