#### Sample size calculation

The sample size calculation is based on our primary outcome endpoint of changes in ICDAS score on the vestibular surfaces of the anterior maxillary teeth in the left and the right quadrants per subject, by comparing the proportion of teeth with worsening ICDAS score in experimental in comparison to the control group. To determine the sample size for each group, a priori power analysis was conducted as follows:
$$ n=\frac{\left(z\frac{\upalpha}{2}+\mathrm{z}\upbeta \right)2\left(p1\left(1-p1\right)+p2\ \left(1-p2\ \right)\right)}{\begin{array}{c}\left(p1-p2\right)2\\ {}\end{array}} $$

*p*1: 8.7% of the lesion incidence in the control group

*p*2: 3.6% of the lesion incidence in the laser group

The data for this power analysis were obtained from a previous study.^9^ The significance level was considered as 95% and power was 80%. By inserting the minimum values in the above formula, the sample size was calculated as 241 teeth (121 teeth per group, i.e., a total number of 41 patients).

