### Assignment of the intervention

#### Sequence generation

A randomization sequence for the allocation of the quadrants will be created using Random Allocation Software. The study is a split-mouth randomized control study and each patient will receive both procedures during the first visit. The patient will be randomized to receive first the laser irradiation and second the placebo procedure or first the placebo procedure and second the laser irradiation before the bonding of the brackets.

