## Conclusion

This randomized control trial is a well-powered, one-center split-mouth experimental study. In split-mouth designs, experimental and control interventions are applied to different areas in the same oral cavity and the advantage is the reduction of the outcome variability estimation, leading to the potential increase in statistical power.

Fixed orthodontic treatment is associated with a high risk of initiation and development of caries lesions. CO_2_-laser has great potential in dental caries prevention. The study outlined in this protocol will be the first direct investigated combination of the preventive effect of the CO_2_-laser irradiation in addition to fluoride therapy and the fixed orthodontic treatment as a risk factor for dental caries. The implementation of CO_2_-laser in the regular protocol for the orthodontic treatment would significantly increase the success of this therapy resulting in lower rates of white spot lesions associated with it.

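### The printed sample size formula gives 345 teeth per group, not 121, so the stated 80% power is unsupported at 41 patients, with or without pairing

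*Protocol article*

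**What the plan says.** The section Sample size calculation bases the size on change in ICDAS score, "by comparing the proportion of teeth with worsening ICDAS score in experimental in comparison to the control group". It prints a formula for the number in each group, with z at alpha/2, and gives two rates: "8.7% of the lesion incidence in the control group" and "3.6% of the lesion incidence in the laser group". On error rates it says "The significance level was considered as 95% and power was 80" per cent; the 95% can only mean a 5% level, and the abstract uses p<0.05. The result is that "the sample size was calculated as 241 teeth (121 teeth per group, i.e., a total number of 41 patients"). The section mentions no correlation between sides and no clustering of teeth.

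Eligibility concerns the "vestibular surfaces of the six maxillary anterior teeth of the permanent dentition", so each patient supplies three teeth per side. On design, the Sequence generation section says "The study is a split-mouth randomized control study and each patient will receive both procedures during the first visit". The Conclusion then states: "This randomized control trial is a well-powered, one-center split-mouth experimental study".

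**The concern.** The formula and all its inputs are printed, so the result can be checked directly, and it comes out nearly three times larger than the number reported. This calculation is the only justification given for 41 patients, and it concerns the primary outcome. If the number is wrong, the stated 80% power and the description of the trial as well powered lose their support, and readers of the eventual result would be working from a false idea of what the trial could detect.

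**Working it through.** **Inputs** (Sample size calculation unless noted)
- p1 = 0.087 (control), p2 = 0.036 (laser), difference d = 0.051
- two-sided alpha = 0.05, z = 1.960; power 80%, z = 0.8416
- three teeth per side (inclusion criteria), so 41 patients give 41 × 3 = 123 teeth per side

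**1. The plan's own formula.** The 2s after the brackets are read as exponents that lost their superscript.
- n per group = (1.960 + 0.8416)² × [p1(1−p1) + p2(1−p2)] / d²
- Variance sum = 0.087 × 0.913 + 0.036 × 0.964 = 0.079431 + 0.034704 = 0.114135
- n = 7.849 × 0.114135 / 0.002601 = 344.4, so **345 teeth per group**, 690 in total, 345 / 3 = 115 patients
- Stated: 121 per group, 241 in total, 41 patients. Not reproduced.

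**2. Attempts to recover 121 or 241.** Teeth per group under other readings:

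| Reading | n per group |
|---|---|
| Pooled variance, two-sided | 348 |
| Pooled, continuity-corrected, two-sided | 386 |
| Arcsine, two-sided | 334 |
| Printed formula, one-sided | 272 |
| Printed formula, z-sum not squared | 122.9 |

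Only the last comes close: 2.8016 × 0.114135 / 0.002601 = 122.9 per group and 245.9 in total. It is an error, not an alternative method, and it does not match the stated figures exactly. Reading 241 as a per-group number gives about 65% power.

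**3. Power at 41 patients by the protocol's formula.**
- Power = Φ(d / √(0.114135 / n) − 1.960)
- n = 123: Φ(0.051 / 0.03046 − 1.960) = Φ(−0.286) = **38.8%**
- n = 121: 38.2%

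**4. Power if teeth are matched left to right.** Two-sided asymptotic McNemar test with discordance π and N pairs:
- Power = Φ([d√N − 1.960√π] / √(π − d²))
- Pairs for 80% = (1.960√π + 0.8416√(π − d²))² / d²

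The documents give no correlation, so the range from none to the maximum is an assumption:

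| Correlation between sides | π | Pairs for 80% | Power at 123 pairs |
|---|---|---|---|
| None | 0.1167 | 350 | 38% |
| Largest these rates allow (about 0.63; no pair with a lesion on the laser side only) | 0.051 | 152 | 71% |

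The exact McNemar test is less favourable: about 29% and 60% at the two ends.

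**5. Clustering.** The three teeth on one side share a mouth. An assumed intraclass correlation of 0.1 in the unpaired formula would raise 345 to 345 × (1 + 2 × 0.1) = 414. The documents give no value; this shows direction only.

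**6. Effect detectable with 80% power at 123 teeth per side, control at 8.7%.** Solving the power expressions for the laser incidence gives about 1.1% unpaired (step 3) and about 2.4% at the most favourable pairing (step 4, π = d). The planning value is 3.6%.

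**The case against.** The strongest defence is the design. The trial is split-mouth, the printed formula is for independent groups, and the Conclusion itself appeals to the reduced variability of within-mouth comparison. On that view 39% is the power of a formula, not of this trial. The section on statistical methods also plans a paired t-test and mixed-effects proportional odds models rather than a comparison of two proportions.

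Much of this stands. A reader might infer that the trial simply has 39% power, that it would miss its target effect more often than it finds it, or that 80% power exists only for a laser incidence near 1.1%. The documents support none of these unconditionally. They give no within-patient correlation; at the favourable limit paired power exceeds one half, and the detectable laser incidence rises to about 2.4%. Nor do they give what would be needed to work out the power of the planned models. A reader might also fault the lack of an attrition margin or predict that a null result will be misread. A condensed article may leave the first to the full protocol, and nothing in it says how a null result would be interpreted.

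The defence does not restore the stated number. Pairing plays no part in the printed calculation, and even at its limit the two-sided test needs 152 pairs against 123. A one-sided McNemar test at that same limit needs about 120 pairs, but it contradicts the printed alpha/2 and assumes that no pair has a lesion on the laser side alone. The lost superscripts are a typesetting or extraction matter, not the error. The text's remark that minimum values were entered is unexplained and does not help, because only one value is given for each input.

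**Conclusion.** The arithmetic error is certain: the printed formula and inputs give 345 teeth per group against the stated 121, a factor of about 2.9 (345 / 121). The stated 80% power and the well-powered claim in the Conclusion are therefore wrong as written.

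The actual power is not known from the documents. It is about 39% under the protocol's independent-teeth formula, and about 38% to 71% for matched pairs across the assumed range of non-negative correlation, with clustering likely to lower it. These figures take the protocol's rates as given and treat the outcome as worsening or no worsening per tooth. The unsquared term remains a conjecture about the cause.

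**What to change.** In Sample size calculation:
- Correct the result to 345 teeth per group (690 teeth, about 115 patients) by the printed formula, with its exponents restored, and state the significance level as 5% two-sided.
- State the power that 41 patients provide as conditional on the assumed within-patient correlation: about 39% under the printed formula, and 38% to 71% for matched pairs before any clustering loss.
- If a detectable effect is given, attach its assumption: 8.7% versus about 1.1% unpaired, or about 2.4% at the most favourable pairing.

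In the Conclusion, delete the description of the trial as well powered. In the reporting plan, commit to an estimate with its confidence interval, and state that a non-significant result does not show absence of effect.

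The cost is wording in a few places and a much less favourable power statement. Whether to revise enrolment is a separate decision for the sponsor. Trial status describes the trial as not yet recruiting, so on this document that decision was still open.

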### Recruitment

The patients at the Department of Paediatric Dentistry of the Faculty of Dental Medicine, Medical University – Plovdiv, Bulgaria, who meet the inclusion criteria, will be screened for eligibility. Once identified, patients will be informed about this research project and will receive information about the possibility of potential study participation. Patient recruitment starts obtaining the full quota of participants within a 1-year time frame. It begins in September 2021 with an estimated enrollment capacity of 4 patients per month.

### Participating centers

The patients are randomly selected from the visitors in the Department of Paediatric Dentistry of the Faculty of Dental Medicine, Medical University – Plovdiv, Bulgaria, and treated in the Laser Centre of the same university.

### Assignment of the intervention

#### Sequence generation

A randomization sequence for the allocation of the quadrants will be created using Random Allocation Software. The study is a split-mouth randomized control study and each patient will receive both procedures during the first visit. The patient will be randomized to receive first the laser irradiation and second the placebo procedure or first the placebo procedure and second the laser irradiation before the bonding of the brackets.

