**Assessments**							
ICDAS score			**×**			**×**	**×**
*SoproLife*® Daylight fluorescence			**×**			**×**	**×**
*SoproLife*® Blue fluorescence			**×**			**×**	**×**

^a^Post-allocation time frame: *t*1, before the start of the treatment; *t*_2_, during laser irradiation/placebo manipulation; *t*_3_, orthodontic treatment; *t*_4_, 6 months after the laser irradiation, *t*_5_, 12 months after the laser irradiation

Due to the nature of the interventions, the doctor, dental assistant, and the patient are not blinded and the trial is an unmasked, open-label trial. The experimental manipulation includes topical fluoride application and CO_2_-laser irradiation of the left maxillary anterior teeth and topical fluoride application (placebo manipulation) to the contralateral teeth of the same patient.

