##### Laser irradiation protocol

The vestibular surfaces of the left maxillary anterior teeth will be exposed to CO_2_-laser (Ultra Dream Pulse, DS_40U, Daeshin Enterprise, Seoul, South Korea), emission wavelength 10,600 nm. The parameter settings used will be:

Time on—100 μs, time off—40 ms;

Average power—0.73 W; peak power—292.73 W;

Speed of movement—2 mm/s;

Energy density with movements—5 J/cm^2^;

Tip-to-tissue distance—20 mm; tip diameter 700 μm; and

Irradiation time—30 s.

The measured values were confirmed using a power meter. The chosen protocol parameters are modified in a previously conducted study [5].

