##### Placebo protocol

The vestibular surfaces of the right maxillary anterior teeth are exposed to sham light (as a placebo light). No pulse energy will be applied.

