#### Participant’s timeline

Each eligible patient undergoes three visits. The first appointment includes screening, consenting and assenting, recording of initial values, topical fluoride application, and treatment with the selected specific parameters of CO_2_-laser of the left maxillary anterior teeth and Placebo procedure for the right, contralateral teeth, and orthodontic treatment at the end of the visit. The second appointment at the 6-month recall includes an oral examination, cleaning of the investigated surfaces, collection of data values, reapplication of the fluoride varnish. The third appointment at the 12-month recall includes an oral examination, cleaning of the investigated surfaces, collection of data values, reapplication of the fluoride varnish.

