#### Blinding

As participants in the treatment as well as the nature of the intervention, the operator and the dental assistant will not be blinded to subjects’ group assignments. The patient will be also not blind to the treatment. The dental assistant will inform the doctor which protocol will be the first to start with and which will be the second protocol. The statistician will be blinded to treatment assignment as data will be masked before the analysis by labeling the 2 quadrants as 0 and 1, without giving the statistician the key.

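### The laser goes on the left in every patient and only the order of the two procedures is randomised, so the laser effect cannot be separated from a left-right difference

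*Protocol article*

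**What the plan says.** Four sections of the protocol article fix the side:

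- Trial design, below Table 1: "CO_2_-laser irradiation of the left maxillary anterior teeth and topical fluoride application (placebo manipulation) to the contralateral teeth of the same patient".
- Laser irradiation protocol: "The vestibular surfaces of the left maxillary anterior teeth will be exposed to CO_2_-laser".
- Placebo protocol: "The vestibular surfaces of the right maxillary anterior teeth are exposed to sham light".
- Participant's timeline, describing what each eligible patient undergoes: laser "of the left maxillary anterior teeth and Placebo procedure for the right, contralateral teeth".

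Three sections describe what is randomised:

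- Sequence generation opens with "A randomization sequence for the allocation of the quadrants will be created", but then defines the randomisation as order: "The patient will be randomized to receive first the laser irradiation and second the placebo procedure", or the other way round.
- Allocation concealment mechanism and implementation says that the sequence in which the two protocols are applied is assigned at random. The envelopes conceal that sequence.
- Blinding has the assistant tell the doctor which protocol comes first and which second, with no mention of side. The statistician is to be masked by "labeling the 2 quadrants as 0 and 1, without giving the statistician the key".

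Statistical methods plans a paired t-test and a mixed-effects proportional odds model. It names no term for side.

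**The concern.** In a split-mouth trial the unit that receives a treatment is the side of the mouth, so the side is what has to be randomised. Here the side is set in advance and chance decides only which procedure is done first in the same visit. That order has no plausible link to lesions found 12 months later.

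Any systematic left-right difference would enter the treatment contrast in full. Examples are brushing hand, plaque, chewing side, operator access and bonding quality. These are general possibilities, not figures from the documents. If they matter, the trial could credit the laser with an effect of side, or miss a real effect, and the comparison of laser with control would not be a randomised one.

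Two safeguards are weakened as well. Sealed envelopes hide nothing about which teeth will be lasered, because that is known before any patient is enrolled. The 0/1 masking would fail if the analysis file carried tooth numbers, because the protocol says which side is the laser side.

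**Working it through.** **1. What varies between patients.** Reading the sections together:

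| Element | Patient drawn as laser first | Patient drawn as placebo first |
|---|---|---|
| Laser side | left | left |
| Control side | right | right |
| Order in the visit | laser, placebo | placebo, laser |

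Only the last row varies. No section describes a patient who gets the laser on the right.

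**2. What the comparison estimates.** Let τ be the laser effect and σ the natural left-minus-right difference.

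- Side fixed: laser minus control has expectation τ + σ in every patient, whatever the number of patients. A side term in the mixed model would be collinear with treatment.
- Side randomised: the expectation is τ + σ or τ − σ with probability ½ each, which averages to τ. With 41 patients split 21/20, the unadjusted remainder is σ × (21 − 20)/41 = σ/41, and a side term removes it.

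**3. The planned effect.** From Sample size calculation: control 8.7%, laser 3.6%, difference 5.1 percentage points. With 41 patients and three teeth per side there are 123 teeth per side (the protocol states 121 per group). Expected lesions are 123 × 0.087 = 10.7 and 123 × 0.036 = 4.4, a difference of about 6 teeth.

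The protocol's 121 per group does not reproduce. Its printed formula gives (1.960 + 0.842)² × (0.087 × 0.913 + 0.036 × 0.964) / 0.051² = 344.4, that is 345 teeth per group. That is a separate problem and does not bear on this point.

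**4. Size of the bias, under assumptions.** The documents give no left-right difference. If σ were 1 point, it would be 1/5.1 = 20% of the planned effect. If it were 3 points, 3/5.1 = 59%.

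**5. False results if the laser did nothing.** Assume a right-side incidence of 8.7%, a left-side incidence of r × 8.7%, 123 teeth per side, independent teeth, and a two-sided 5% two-proportion test (a simplification of the planned analysis). The chance of a significant result favouring the laser is Φ((Δ − 1.96·s₀)/s₁). Here Δ is the difference, s₀ the pooled standard error and s₁ the unpooled one.

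| r (left/right) | Spurious difference (points) | Chance of a false result for the laser |
|---|---|---|
| 0.9 | 0.9 | 4.3% |
| 0.8 | 1.7 | 7.3% |
| 0.7 | 2.6 | 11.9% |
| 0.6 | 3.5 | 18.7% |

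The nominal value is 2.5%. A side difference in the other direction hides a true effect. With laser incidence 3.6% and r = 1.25, the expected difference falls to 8.7 − 4.5 = 4.2 points. With r = 1.5 it falls to 8.7 − 5.4 = 3.3 points.

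**The case against.** The strongest reply is that the protocol contradicts itself rather than plainly fixing the side. Sequence generation speaks of allocating quadrants, the Blinding section withholds a key linking quadrants to treatment, and the trial is called randomised throughout. Side randomisation may have been intended. This stands as a statement about intention, but it does not rescue the text. The same paragraph goes on to define the randomisation as order, and four sections tell the operator to laser the left. On either reading, something at the core of the design is wrong as written.

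Other points in the plan's favour:

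- All six teeth must be ICDAS 0 at entry, and developmental defects are excluded. This removes visible imbalance at baseline, but not side differences that arise during 12 months with brackets.
- The documents give no left-right difference, so the 1 to 3 points and the ratios above are illustrations. Zero is possible. This is accepted. The confounding does not depend on the value, but no actual bias has been shown.
- A statistician given only 0 and 1 does not know which label is left. This is also accepted. Masking fails only if tooth numbers or side labels reach the file.
- Table 1 puts allocation before the baseline scores, but Clinical protocol records them before the chosen method is applied. The column order alone does not show that envelopes are opened early.

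**Conclusion.** The concern holds. As written, laser and left side coincide in every patient, and randomising procedure order balances only order effects. The estimated effect is the laser effect plus the side effect, and neither the paired t-test nor the mixed model can separate them. More patients would not help.

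The size of the bias is unknown. Side differences of 1 to 3 points, which are assumed, would amount to 20% to 59% of the planned 5.1 points. Under the simplifying assumptions above, left/right ratios from 0.9 to 0.6 would raise the chance of a false result for the laser from 2.5% to between 4.3% and 18.7%.

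The conclusion rests on the fixed-side text, which has much the heavier support. If the quadrant is in fact to be randomised, the four fixed-side sections are wrong and have to be changed. This must be fixed before the first patient is treated, because analysis cannot repair it afterwards.

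**What to change.** - Randomise which quadrant, left or right, receives the laser, in balanced blocks, with the same software and the same sealed envelopes. Procedure order can still be randomised as well.
- Reword Trial design, Laser irradiation protocol, Placebo protocol, Participant's timeline and Sequence generation so that they refer to the quadrant allocated to laser and the quadrant allocated to control.
- State that the envelope is opened only after the baseline ICDAS and SoproLife scores are recorded, and make Table 1 agree.
- Include side as a fixed effect in the model. It becomes estimable once side is randomised.
- Give the statistician coded treatment labels without tooth numbers or side.

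The cost is protocol wording and a new randomisation list, with no extra patients, visits or staff. The one drawback is that the operator must check the allocated side for each patient. The article reports that recruitment has not begun, so the change can be made before any patient is affected.
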